###### HAM-4-mTBI

The HAM-4-mTBI (42) is a condensed, hybrid mobility assessment based on the Functional Gait Assessment (FGA) (47) and the High-Level Mobility Assessment Tool (HiMAT) (48) to monitor individuals with mTBI. Participants will complete the FGA gait with horizontal head turns and gait with pivot turn, as well as the HiMAT fast forward and backward walk. Outcomes measured from the HAM-4-mTBI will include the Opal-based measures plus the FGA gait with horizontal head turns and gait with pivot turn scored according to FGA criteria (scored 0 to 3) and the HiMAT fast forward and backward walk scored according to HiMAT criteria (middle 10 m of a 20 m trial is timed, scored 1 to 4).

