##### Readiness Assessment Battery

All participants will undergo an assessment battery that includes the 4-Item Hybrid Assessment of Mobility for mild Traumatic Brain Injury (HAM-4-mTBI) (42), modified version of the Portable Warrior Test of Tactical Agility (POWAR-TOTAL) (43, 44), 5-10-5 Shuttle Run (45), and 300-yard Shuttle Run (45, 46) tests. Opal inertial sensors and Mobility Lab software (APDM™ wearable technologies, Portland, OR) will be used for all assessments to record objective outcomes. The Opal inertial sensors are worn on the forehead, sternum, lumbar spine, non-dominant wrist, and dorsum of each foot during the assessment battery. Opal-based outcome measures will include: peak lumbar turning speed (peak angular rate of the pelvis in the transverse plane); head turning speed (peak angular rate of the head in the transverse plane); upper trunk turning speed (peak angular rate of the upper trunk in the transverse plane); head-body coordination timing (peak angular displacement between the head and the trunk measured just before or at the onset of trunk axial rotation during turning, measured in the transverse plane); and head turn symmetry (left-to-right head turn velocity ratio).

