###### Modified Version of the Portable Warrior Test of Tactical Agility (POWAR-TOTAL)

During the modified version of the POWER-TOTAL (43, 44), the participant will carry a simulated standard service weapon (Bluegun M4). The participant begins the test in a prone position (Figure 1). They will then stand up, run diagonally left/forward for 3 m, drop back into a prone position on a floor mat and perform a clockwise combat roll. Afterward, they will stand and backpedal to the starting position, side-shuffle to the left, run diagonally right/forward for 3 m, drop back into a prone position on a floor mat and perform a counterclockwise combat roll, stand up and backpedal to the starting line, and side-shuffle to the right to end at the starting position. The time taken to complete the single-task modified version of the POWAR-TOTAL will be used to determine the interval for the cognitive-only single-task. Specifically, the participant is told an 8-digit grid coordinate, the stopwatch is started immediately after the final digit is spoken, the duration equivalent to the single-task POWAR-TOTAL completion time is waited, and then the participant is asked to recall the grid coordinate. Then, this cognitive task is combined with the physical task for a cognitive dual-task paradigm where the participant must remember an 8-digit grid coordinate; immediately upon completion of the modified version of the POWAR-TOTAL the participant will be asked to recall the 8-digit grid coordinate. Outcomes measured from the modified version of the POWAR-TOTAL will include the Opal-based measures plus the time to complete the single-task trial, time to complete the dual-task trial, and cognitive task accuracy during the single-task (cognitive) and dual-task (physical + cognitive) trials (percentage of correct responses).

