###### 5-10-5 Shuttle Run

A part of the Ranger Athlete Warrior (RAW) assessment battery, participants will run five yards (4.57 m) to the right, turn and run 10 yards (9.14 m) to the left, then turn and run 5 yards (4.57 m) back through the starting position (Figure 2). This test of agility and quickness is then repeated in the opposite direction (to the left). Outcomes measured from the 5-10-5 Shuttle Run (45) will include the Opal-based measures plus the time to complete the trial to the right, and time to complete the trial to the left.

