#### Relationships between neuroimaging changes and behavioral outcomes

Correlation analyses will be performed to examine the relationships between rs-fMRI findings and behavioral outcomes (from questionnaires and the Readiness Assessment Battery tasks: HAM-4-mTBI, modified version of the POWAR-TOTAL, 5-10-5 Shuttle Run, and 300-yard Shuttle Run), as well as clinical characteristics, with a significance threshold set at *p* < 0.05.

By comparing the behavioral outcomes from questionnaires and the Readiness Assessment Battery between baseline and post-rehabilitation, this study aims to identify any significant changes occurring between these assessment points. To compare between-group differences in behavioral outcomes, improvements during the 4-week intervention will be calculated by subtracting the baseline value (the first visit) from the post-rehabilitation value. A general linear model will be used to assess between-group differences in primary and secondary outcomes. Estimated marginal means, standard errors (SEs), 95% confidence intervals, and effect sizes will be reported for the outcomes derived from the general linear model. Effect sizes will be interpreted as small (0.01), medium (0.06), and large (0.14) (62). The Minimum Clinically Important Difference (MCID) will be calculated for all outcomes using the equation MCID = SD ^*^ 0.2.

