## Discussion

After mTBI, SMs often have vestibular and ocular deficits that impair their ability to perform critical tasks essential for military readiness and operational effectiveness (8). While overt balance and mobility deficits typically resolve within a few days (63), abnormalities can persist and can be missed in routine clinical assessments. These lingering deficits have been identified using advanced instrumentation and analytical methods (64–72). These residual deficits, particularly in complex, real-world tasks, can compromise the overall performance and safety of SMs in demanding operational environments (3, 5). Despite a growing recognition of the importance of addressing vestibular dysfunction in post-mTBI rehabilitation, there remains a significant gap in understanding the best strategies to mitigate these impairments, especially when it comes to rehabilitation dosage.

Current rehabilitation techniques are not consistently supported by strong evidence, and the VA/DoD Clinical Practice Guidelines (CPGs) do not provide clear recommendations for optimal rehabilitation dosages or strategies (25). Access to specialized care may be limited at military treatment facilities without dedicated resources, such as Intrepid Spirit Centers. Traditional assessments, which often rely on single-task evaluations, may lack the sensitivity to detect subtle, lingering deficits (73, 74). Furthermore, current RTD decisions typically rely on self-reported symptoms and standardized physical and cognitive tests, which may not accurately reflect the functional demands of military activities (6–9), limiting their ability to drive tangible improvements in operational performance. This ambiguity presents a clear need for more comprehensive, objective, and ecologically valid rehabilitation interventions that can better capture and address the multifaceted impairments experienced by SMs with mTBI.

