The Praxis study aims to fill this gap by investigating the potential benefits of a novel VR-based rehabilitation system designed specifically for SMs with mTBI-related vestibular complaints. By integrating real-world, military-relevant tasks within a multisensory framework, the Praxis system provides an engaging rehabilitation tool with face validity that simulates some of the sensory, motor, and cognitive demands SMs face in operational settings. Moreover, increasing the complexity of rehabilitation tasks, such as incorporating dual-task elements, may reveal subtle abnormalities that traditional, simpler assessments fail to detect (73–76). This could improve clinical decision making, particularly for RTD assessments, by providing more nuanced and objective measures of functional recovery (77).

Wearable sensors embedded in the Praxis system allow for the continuous monitoring of complex motor tasks, such as turning, which is an ecologically relevant action frequently performed by SMs (22). Recent developments in wearable technology have made it possible to conduct objective and sensitive evaluations of subtle motor impairments during routine clinical assessments (78–81). These objective assessments, free from the limitations of arbitrary ceiling effects, enable precise tracking of rehabilitation progress and functional outcomes (77). If the findings from this study demonstrate that the Praxis system is effective, it could offer new evidence for revising the VA/DoD CPGs to include VR- and sensor-based technologies as standard components of vestibular rehabilitation after mTBI.

Moreover, the Praxis system could lead to more consistent and evidence-based decision making regarding RTD determinations by providing rehabilitation protocols that are not only responsive to rehabilitation but also directly associated with performance in real-world tasks. Should the Praxis system prove effective, it could motivate widespread adoption of such technologies in post-mTBI rehabilitation, potentially guiding future policy updates and clinical protocols.

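### The two HAM-4-mTBI fast walks are timed, but only a 1-to-4 category is listed as their outcome, which leaves out information already collected

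*Protocol article*

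**What the plan says.** The HAM-4-mTBI section introduces its outcome list with "Outcomes measured from the HAM-4-mTBI will include the Opal-based measures plus the FGA gait with horizontal head turns" and then adds the FGA pivot-turn item and the two HiMAT walks. The walks enter the list as "HiMAT fast forward and backward walk scored according to HiMAT criteria (middle 10 m of a 20 m trial is timed, scored 1 to 4". Neither seconds nor speed is listed for them.

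The other timed tests in the same battery are handled differently. The modified POWAR-TOTAL outcomes "will include the Opal-based measures plus the time to complete the single-task trial, time to complete the dual-task trial". The 5-10-5 Shuttle Run outcomes "will include the Opal-based measures plus the time to complete the trial to the right, and time to complete the trial to the left". The 300-yard Shuttle Run section likewise lists single-task and dual-task completion times.

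The sensor measures that accompany every test are defined under Readiness Assessment Battery: "Opal-based outcome measures will include: peak lumbar turning speed (peak angular rate of the pelvis in the transverse plane", followed by head turning speed, upper trunk turning speed, head-body coordination timing and head turn symmetry.

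Under Relationships between neuroimaging changes and behavioral outcomes, "improvements during the 4-week intervention will be calculated by subtracting the baseline value (the first visit) from the post-rehabilitation value". Between-group differences go to a general linear model, battery outcomes are correlated with the rs-fMRI findings, and the MCID for every outcome is set at 0.2 times the SD.

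**The concern.** A continuous measurement is taken and then listed only in a coarser form. The sensor measures do not make up for this: all five concern turning or head-trunk movement, and the two walks as described contain no turn. The category is thus the only listed outcome that reflects walking speed for two of the four HAM-4-mTBI items.

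A four-level score loses information in two ways. Changes that stay within a category disappear, and a participant at 4 cannot improve. Both losses carry through to the change scores, the between-group model and the correlations with rs-fMRI change and Praxis scores. For a pilot meant to supply effect sizes for later trials, this costs precision without saving any effort, because the stopwatch time has already been taken.

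**Working it through.** The plan states no power, cut-points, walk times or SDs for these items, so there is no figure of its own to reproduce. Step 1 uses the document alone. Steps 2 and 3 use assumed inputs.

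**Step 1. Score step against the protocol's MCID.**
- Inputs: score range 1 to 4 (HAM-4-mTBI section); MCID = 0.2 × SD (Relationships section); n = 15 (Sample size and justification).
- The SD is largest when participants split between 1 and 4. With an even split it is (4 − 1)/2 = 1.5.
- As a sample SD at n = 15 with 7 at one end and 8 at the other: variance = 9 × (7 × 8/15²) × (15/14) = 2.40, so SD = 1.55.
- MCID is therefore at most 0.2 × 1.5 = 0.30, or 0.2 × 1.55 = 0.31 point.
- The smallest non-zero individual change is 1 point, and 1/0.31 = 3.2. The step is at least about 3 times the MCID.
- This concerns individual resolution. A group mean can still move by 0.3 point.

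**Step 2. Share of participants whose category does not change after a real gain.**
- Assumed: baseline time is normal with SD 1, everyone gains d SD, and there are three cut-points.
- Well-spread layouts: quartile cuts (−0.674, 0, 0.674), cuts 1 SD apart (−1, 0, 1) and cuts 1.5 SD apart (−1.5, 0, 1.5).
- Ceiling layouts: 50% in the top category at baseline (0, 1, 2) and 80% in it (0.84, 1.84, 2.84).
- 400,000 simulated participants.

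| True gain | Well-spread cuts | 50% at top | 80% at top |
|---|---|---|---|
| 0.2 SD | 79-87% | 87% | 94% |
| 0.5 SD | 50-67% | 70% | 87% |
| 0.8 SD | 32-48% | 57% | 82% |
| 1.0 SD | 18-36% | 50% | 80% |

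**Step 3. Power, time against score.**
- Assumed: n = 15, paired t-test, two-sided 0.05, and follow-up = baseline − d + noise with SD 0.7, so the SD of change is 0.7 baseline SD.
- Same cut-points; 4,000 simulated trials per setting.

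| True gain | Time | Score, well-spread cuts | Score, 50% at top | Score, 80% at top |
|---|---|---|---|---|
| 0.2 SD | 17-19% | 11-12% | 5% | 2% |
| 0.5 SD | 72% | 43-48% | 22% | 4% |
| 0.8 SD | 98-99% | 83-87% | 52% | 10% |

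The loss at 0.5 SD is substantial even with no concentration at the top. The very low values appear only when most participants are assumed to start there.

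**The case against.** **The score follows the cited instrument, and the list is not closed.** Using HiMAT's own criteria is not an error, the outcomes are introduced as things the assessment will include, and nothing says the seconds are thrown away. This stands as a reason to keep the score. It does not answer the point, because the same kind of wording introduces the lists for the other timed tests, and there the time is named. The article does not leave this outcome open: it states one, in the coarser form.

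**A reader might infer that most real changes in walking speed would score as no change, that the change scores would be near-constant, and that power would be close to zero.** The documents do not support this. They give no cut-points, baseline times or expected change. With well-spread cuts, most participants do change category at a gain of 0.8 SD. The near-zero power figures need a heavy ceiling. Such a ceiling is plausible: participants come from a special operations performance programme, also sprint and perform combat rolls, and need no walking deficit to enter. The Discussion adds that "While overt balance and mobility deficits typically resolve within a few days (63), abnormalities can persist and can be missed in routine clinical assessments". But Praxis participants must have ongoing dizziness or imbalance, the programme includes musculoskeletal injury rehabilitation, and only severe pain excludes. Fast or backward walking could well be impaired at entry.

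**A reader might also see a contradiction with the Discussion**, which says "These objective assessments, free from the limitations of arbitrary ceiling effects, enable precise tracking of rehabilitation progress and functional outcomes (77". That sentence follows one on wearable technology and describes sensor-based assessment. It makes no claim about HiMAT item scores.

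**The power comparison uses a test not assigned to these items.** Under Usability and effectiveness of the Praxis system, paired t-tests are named only for questionnaires. Battery outcomes go to a general linear model and correlations, which were not simulated, and the planned false-discovery-rate correction was not applied. This stands. The figures illustrate the loss from categorising and do not predict the trial's power.

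**The impact is small.** These are two items of one test in a four-test battery, in a feasibility-sized pilot whose stated success criteria are a mean SUS of at least 68 and 80% session completion. This also stands.

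**Conclusion.** The point holds as a modest, correctable choice of outcome. The article times both walks, lists only the 1-to-4 category for them, lists time for every other timed test, and defines no sensor measure that recovers walking speed.

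Two consequences need no assumption about walk times or cut-points: a participant already at 4 who walks faster scores a change of 0, and one score step is at least about 3 times the protocol's own MCID, taking the SD in that rule as the SD of the score.

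The power loss is conditional. For a 0.5 SD gain with n = 15 and a paired test, it is about 72% on time against about 43-48% on the score if cut-points are well spread, and 22% or 4% if half or 80% start at the top. The actual share at the top is unknown. No primary success criterion is affected.

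**What to change.** In the HAM-4-mTBI section, list the 10 m time in seconds (or speed, 10 m divided by the time) for the fast forward walk and the backward walk as outcomes beside the HiMAT score. Use the time or speed in the change-score, between-group and correlation analyses. Report the HiMAT category descriptively, with the number of participants at the maximum at baseline and at 4 weeks, so that any ceiling becomes visible.

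The cost is one sentence. The times are already taken, so no procedure, visit or staff time is added. The small downside is two more continuous outcomes in the false-discovery-rate correction. That disappears if they replace the category scores in the inferential analyses, as proposed here. If seconds are used, note that a negative change is then a gain, as it already is for the other timed tests.

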###### Modified Version of the Portable Warrior Test of Tactical Agility (POWAR-TOTAL)

During the modified version of the POWER-TOTAL (43, 44), the participant will carry a simulated standard service weapon (Bluegun M4). The participant begins the test in a prone position (Figure 1). They will then stand up, run diagonally left/forward for 3 m, drop back into a prone position on a floor mat and perform a clockwise combat roll. Afterward, they will stand and backpedal to the starting position, side-shuffle to the left, run diagonally right/forward for 3 m, drop back into a prone position on a floor mat and perform a counterclockwise combat roll, stand up and backpedal to the starting line, and side-shuffle to the right to end at the starting position. The time taken to complete the single-task modified version of the POWAR-TOTAL will be used to determine the interval for the cognitive-only single-task. Specifically, the participant is told an 8-digit grid coordinate, the stopwatch is started immediately after the final digit is spoken, the duration equivalent to the single-task POWAR-TOTAL completion time is waited, and then the participant is asked to recall the grid coordinate. Then, this cognitive task is combined with the physical task for a cognitive dual-task paradigm where the participant must remember an 8-digit grid coordinate; immediately upon completion of the modified version of the POWAR-TOTAL the participant will be asked to recall the 8-digit grid coordinate. Outcomes measured from the modified version of the POWAR-TOTAL will include the Opal-based measures plus the time to complete the single-task trial, time to complete the dual-task trial, and cognitive task accuracy during the single-task (cognitive) and dual-task (physical + cognitive) trials (percentage of correct responses).

**Figure 1 F1:**
[figure not shown]
Schematic of the modified version of the Portable Warrior Test of Tactical Agility (POWAR-TOTAL). The service member begins the test in prone (pictogram) and follows the path direction of the (yellow) arrows. Combat rolls are performed on a folding tumbling mat (blue rectangle).

###### 5-10-5 Shuttle Run

A part of the Ranger Athlete Warrior (RAW) assessment battery, participants will run five yards (4.57 m) to the right, turn and run 10 yards (9.14 m) to the left, then turn and run 5 yards (4.57 m) back through the starting position (Figure 2). This test of agility and quickness is then repeated in the opposite direction (to the left). Outcomes measured from the 5-10-5 Shuttle Run (45) will include the Opal-based measures plus the time to complete the trial to the right, and time to complete the trial to the left.

**Figure 2 F2:**
[figure not shown]
Schematic of the 5-10-5 Shuttle Run to the right. The service member begins the test in the middle and follows the path direction of the (yellow) arrows.

###### 300-yard Shuttle Run

As part of the RAW assessment battery, participants will run 25 yards (22.86 m), turn, and run 25 yards (22.86 m) back, completing this sequence six times for a total of 300 yards (274.32 meters; Figure 3). Participants must not use a circular path when making turns. The time taken to complete the single-task 300-yard Shuttle Run will be used to determine the interval for the cognitive-only single-task. Specifically, the participant is told an 8-digit grid coordinate, the stopwatch is started immediately after the final digit is spoken, the duration equivalent to the single-task 300-yard Shuttle Run (45, 46) completion time is waited, and then the participant is asked to recall the grid coordinate. Then, this cognitive task is combined with the physical task for a cognitive dual-task paradigm where the participant must remember an 8-digit grid coordinate; immediately upon completion of the 300-yard Shuttle Run the participant will be asked to recall the 8-digit grid coordinate. Outcomes measured from the 300-yard Shuttle Run will include the Opal-based measures plus the time to complete the single-task trial, time to complete the dual-task trial, and cognitive task accuracy during single-task (cognitive) and dual-task (physical + cognitive) trials (percentage of correct responses).

**Figure 3 F3:**
[figure not shown]
Schematic of the 300-yard Shuttle Run. The service member follows the path direction of the (yellow) arrows six times down and back.

##### Resting-state functional MRI (rs-fMRI; Praxis group only)

Only participants in the Praxis group will undergo this assessment. With a Siemens 3T scanner (MAGNETOM Skyra Fit), anatomical and functional scans will be performed during each MRI session, alongside localizer scans. The acquisition parameters will follow established guidelines and standard methodologies to ensure comparability with previous studies. To this end, the team will closely mimic published protocols (14, 49), with the anatomical acquisition for co-registration intended to use magnetization-prepared rapid acquisition gradient echo (MPRAGE) imaging. The functional echo-planar imaging (EPI) sequence parameters will be selected to closely align with those used in prior research (14), including a repetition time (TR)/time to echo (TE) of 2,130 ms/30 ms, a field of view (FoV) of 220 mm x 220 mm, a voxel size of 3.4 mm x 3.4 mm x 3.4 mm, an axial slice number of 39, and a volume count of 245, with an expected rs-fMRI scan time of ~8.7 min. The rs-fMRI outcomes include functional connectivity (FC), regional homogeneity (ReHo), and fALFF, which will be analyzed to assess neurophysiological changes post-rehabilitation.

